### Sample size

2.3

The power calculation is based on results from strength training effects in prostate cancer patients on androgen deprivation therapy, the Physical Exercise and Prostate Cancer trial (PEPC trial).^[10]^ With a similar effect on muscle fiber size (+898 ± 840 μm^2^), we need 10 participants in each group to get a statistical power of 80% in the present study, to further enhance the power up to 95%, we need 16 participants in each group. Consequently, 50 participants (25 in each arm) will be recruited to account for drop-outs during the intervention. The power calculation is based on the PEPC trial^[10]^ but findings from the study by Mijwel and colleagues^[13]^ strongly support similar expectations in breast cancer patients on chemotherapy.

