### Study design

2.1

This study is a two-armed randomized controlled trial with follow-up at 6 months (Fig. 1). Data will be collected before the first cycle of chemotherapy (T0), after chemotherapy (T1), and 6 months later (T2). The primary outcome for this study is muscle fiber size. Secondary outcomes are: regulators of muscle fiber size and function, indicators of cellular stress and mitochondrial function, myokines with potential antitumor effects, muscle strength, and cardiorespiratory fitness. All outcomes are listed in Table 1.

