### Randomization

2.4

After completion of baseline measurements, participants will be randomized by research staff in a 1:1 ratio to either the *intervention group* (supervised heavy-load RT during chemotherapy treatment) or to the *control group* (activity as usual during chemotherapy treatment), stratified on treatment (neo-adjuvant or adjuvant treatment). Sealed envelopes will be used to conceal the group allocation.

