### Statistical analyses

2.11

Data will be analyzed according to the intention-to-treat principle. Analyses will include standard descriptive statistics, *t* tests, correlation, regression and two-way repeated-measures ANOVA or the comparable nonparametric test as necessary to examine differences between and within groups, at T0, T1, and T2. In addition, a per-protocol analysis, that is, adherence to the protocol, will be conducted. Should imbalances in important variables be detected, sensitivity analyses will also be added including these as covariates in the model. All data will be cleaned and quality-checked before analysis.

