## Discussion

3

The present study aims to investigate the effects of a heavy-load resistance-training program on skeletal muscle cellular outcomes in women diagnosed with breast cancer undergoing chemotherapy. The results are expected to provide insights about the mechanism involved in side effects of chemotherapy on skeletal muscle. Such knowledge can be used to design effective physical exercise programs to support individuals with breast cancer during and following chemotherapy and possibly reduce long-lasting side effects such as impairments in physical function, fatigue, and risk for comorbidities.

To our knowledge, this will be the first randomized controlled study evaluating heavy-load RT during (neo-)adjuvant chemotherapy treatment in breast cancer patients to explore its effects on muscle cellular outcomes in a relatively larger study population in comparison to previous studies.^[13,33,34]^ Although the primary outcome of this present study is muscle fiber CSA, we are also including a wide range of biological measurements, including specific proteins involved in skeletal muscle hypertrophy/degradation and regulators of muscle fiber function. These analyses will provide further insight into the underlying mechanism through which chemotherapy affects muscle tissue and how RT could be used as a therapeutic measure to counteract immediate and long-term treatment side effects. As exercise has been suggested to have an antitumor effect^[26]^ regular exercise could have a positive effect on the recurrence rate. In this study, we will investigate changes in myokines with potential antitumor effect in both muscle tissue and blood and these results will give valuable insight to exercise-induced antitumor mechanisms. However, the possible effect on cancer recurrence rate has to be further explored in future longitudinal studies as our study will only include follow-up measures at 6 months post end of treatment. Importantly, the feasibility of the training program has been confirmed by a previous study (Phys-Can study)^[29]^) in which ∼75% of participants completed the 6-month training program with an exercise adherence of approximately 67%.

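### The stated sample sizes (10 per group for 80% power, 16 for 95%) do not follow from the stated effect of +898 ± 840 μm² in a two-arm comparison, so the drop-out margin over the 95% target is about 1 per arm, not 9

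*Protocol article*

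**What the plan says.** The Sample size section of the protocol article borrows its effect from a strength-training trial in prostate cancer patients: "With a similar effect on muscle fiber size (+898 ± 840 μm^2". From this it states that "we need 10 participants in each group to get a statistical power of 80% in the present study", and "to further enhance the power up to 95%, we need 16 participants in each group". It then moves to the recruitment target: "50 participants (25 in each arm) will be recruited to account for drop-outs during the intervention". The section gives no alpha, sidedness, test or drop-out rate. It does not say whether 898 is a difference between arms or a change within one arm, or what the ± denotes.

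The design is parallel. Under Study design, "This study is a two-armed randomized controlled trial with follow-up at 6 months". Under Randomization, "participants will be randomized by research staff in a 1:1 ratio". The Statistical analyses section lists t tests, correlation, regression and "two-way repeated-measures ANOVA or the comparable nonparametric test as necessary to examine differences between and within groups". It mentions covariates only for sensitivity analyses, should imbalances be found.

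**The concern.** The section prints both the inputs and the results of its power calculation, so a reader can check one against the other. For two independent groups they do not agree. The stated sizes are about a third too small on the usual reading: 10 against 15, and 16 against 24.

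Two things are at stake. First, the recruitment target is derived from the 16 per group, so 25 per arm appears to leave 9 spare participants per arm for losses. If 24 are needed for 95% power, nearly all of that reserve is already used before anyone drops out. Second, this is the article's only justification of power for the primary outcome. A null result would be read against a claimed 95% chance of detecting the effect with 16 per group, when that chance was lower.

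**Working it through.** **Inputs.** Effect 898 μm² and ± 840 μm², 10 per group for 80%, 16 per group for 95%, and 25 recruited per arm (all from Sample size). Two arms, 1:1 (Study design; Randomization). Assumed because not stated: two-sided alpha of 0.05, ± is an SD, and 898 is the between-group difference with 840 the common SD.

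**Standardized difference.** d = 898 / 840 = 1.069, so d² = 1.143.

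**Attempt to reproduce the plan's figures, normal approximation.** n per group = 2(z₁₋α/₂ + z₁₋β)² / d².
- 80%: 2 × (1.960 + 0.842)² / 1.143 = 13.7, so 14.
- 95%: 2 × (1.960 + 1.645)² / 1.143 = 22.7, so 23.

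**Exact two-sample t test.** Power comes from the noncentral t distribution with 2n − 2 degrees of freedom and noncentrality d√(n/2). For n = 10, the noncentrality is 2.390 and the critical value 2.101. For n = 16 they are 3.024 and 2.042.

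| Evaluable per arm | Power (two-sided 5%) |
|---|---|
| 10 | 61.9% (stated 80%) |
| 14 | 77.7% |
| 15 | 80.7% |
| 16 | 83.3% (stated 95%) |
| 19 | 89.4% |
| 23 | 94.4% |
| 24 | 95.2% |
| 25 | 95.9% |

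The smallest sizes that reach 80% and 95% are therefore 15 and 24 per group.

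**Other routes to 10 and 16.**
- *One-sided 5%, two-sample t:* 12 and 20. Power is 74% at 10 and 90% at 16, so the 95% figure still fails.
- *Paired or one-sample t, two-sided:* 9 and 14. With d rounded to 1.0 it gives exactly 10 and 16. This comes closer, but it tests a change within one group and does not power a comparison between arms.
- *Solving backwards (two-sided two-sample t):* 10 per group at 80% needs d = 1.325, and 16 per group at 95% needs d = 1.318. With the effect held at 898, the SD would be about 680 (898/1.325 = 678; 898/1.318 = 681). With the SD held at 840, the effect would be about 1,110 (1.325 × 840 = 1,113; 1.318 × 840 = 1,107). The section states neither.

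**Drop-out margin.** As stated it is 25 − 16 = 9 per arm (9/25 = 36%). As recomputed it is 25 − 24 = 1 per arm, and losing 2 per arm already takes power below 95%. With an assumed 25% loss in both arms (25 × 0.75 = 18.75, about 19), power is about 89%. With 19 evaluable in the training arm and all 25 in the control arm, it is 92.9%. For 80% power the margin is 25 − 15 = 10 per arm (40%).

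**The case against.** The strongest reply is that the two stated sizes imply almost the same d (1.325 and 1.318). That looks like one coherent calculation with an input left out of a condensed article. Several such inputs would serve:
- *Baseline adjustment.* A correlation of about 0.6 gives an effective d of 1.069/√(1 − 0.36) = 1.336, which yields 10 and 16.
- *Unequal SDs.* If 840 is the trained arm's SD and the control arm's is about 460, the average-variance SD is √((840² + 460²)/2) = 677, and d is 1.326.
- *A declining control arm.* The first hypothesis expects fiber size to fall under chemotherapy. A control loss of about 210 would make the difference about 898 + 210 = 1,108, and d about 1.32.

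These are fair possibilities, and because of them 15 and 24 cannot be called the true figures without conditions. None of them rescues the section as written, since no correlation, control-arm SD or control-arm change is stated. Baseline adjustment has a further difficulty: if +898 ± 840 is a change with its own SD, the within-person correlation is already reflected in that SD.

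A reader might also infer that the trial misses its power under its own expected attrition, because the Discussion reports about 75% completion and about 67% adherence. The document does not support this. Those figures describe an earlier 6-month programme and are cited for feasibility; this intervention lasts about 16 weeks, and Sample size sets no loss rate. Not finishing a training programme is also not the same as lacking a biopsy. Shrinking the effect by 0.75 or 0.67 goes further still. It assumes that non-completers gain nothing or that benefit is proportional to adherence, and that the borrowed effect came from full adherence.

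Finally, the match of a paired calculation to 10 and 16 at d = 1.0 is suggestive, but it does not show that this is what was done.

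**Conclusion.** The point holds: for the two-arm comparison that the article describes, 10 and 16 per group cannot be obtained from the effect it prints. This is a disagreement between stated inputs and stated results, not a detail left to a fuller document. The replacement figures of 15 and 24 rest on two-sided 5%, ± as an SD, and 898 as the between-group difference. The failure of the 95% figure does not depend on sidedness.

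The consequence is limited. The claimed power at the stated sizes is too high by about 18 percentage points at 10 per group and 12 at 16, and the reserve over the 95% target nearly disappears. On the same reading the trial is not badly underpowered: 25 per arm gives 96% with no losses, and power stays above 80% down to 15 evaluable per arm. Calling the trial too small would go beyond what the document shows.

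**What to change.** Keep 50 participants and rewrite the Sample size paragraph.

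1. State alpha, sidedness and the test. State whether 898 ± 840 is a between-group difference in change or a one-arm change, and that the ± is an SD if it is.
2. Then either correct the sizes to 15 per group for 80% and 24 per group for 95%, or give the inputs (between-group difference, SD or baseline correlation) from which 10 and 16 can be reproduced.
3. Report power at 25 per arm (96% on the reading above) and at plausible evaluable numbers, for example about 89% at 19 per arm, labelled as an assumed 25% loss.

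The cost is one paragraph and a less favourable power statement. No extra patients are needed and the design does not change.

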### Randomization

2.4

After completion of baseline measurements, participants will be randomized by research staff in a 1:1 ratio to either the *intervention group* (supervised heavy-load RT during chemotherapy treatment) or to the *control group* (activity as usual during chemotherapy treatment), stratified on treatment (neo-adjuvant or adjuvant treatment). Sealed envelopes will be used to conceal the group allocation.

### Intervention

2.5

Participants in the intervention group will perform supervised heavy-load RT twice a week from the week following T0 and throughout the course of treatment with chemotherapy, approximately 16 weeks. Sessions will be performed at a public gym and led by trained coaches. The following 6 exercises will be included in the program: seated leg-press, seated chest-press, seated leg-curl, seated row and seated leg-extension performed in machines and seated overhead-press using dumbbells. Completed training (weight lifted, number of repetitions and sets) and rating of perceived exhaustion will be documented by the participants in training logbooks. The scheduled timeframe of the training is described in Table 2. Briefly, the first 2 weeks of the program represent familiarization to the training protocol, tests, and Omni-scale for self-reported perceived exertion.^[27]^ During this period, the participants will perform exercises at a light load. After the first 1 RM-test (1 repetition maximum test), training will progress in sets and training load before testing of 6- and 10 RM which will provide the participants with individualized loads. Rest periods between sets will be 2 (6 RM training load) and 1 minute (10 RM training load) for the 2 different sessions, respectively. The training load will be adjusted throughout the intervention period. Participants in the control group are encouraged to continue with their activity as usual that is, maintain their habitual physical activity level and not initiate RT during chemotherapy. To increase interest in participation, controls will be invited to a 2-week introduction to the same resistance-training program as the intervention group following completion of chemotherapy and offered a 12-month membership at a local gym, free of charge.

**Table 2 T2:** Overview of the resistance training intervention.

Week	Training session 1	Training session 2
1	1×20 sub-maximal load Focus on correct technique	1×20 sub-maximal load Focus on correct technique
2	2×10 sub-maximal load	1RM-test
3–4	2×10 sub-maximal load	2×10 sub-maximal load
5	Test of 10RM	Test of 6RM
6	2×10 RM	2×6 RM
7–15	3×10 RM	3×6RM
16	3×10RM	1RM-test

RM = repetition maximum.

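### Because controls are offered the same training after chemotherapy, T2 compares early with delayed access to resistance training; the plan should make T1 primary and label T2 accordingly

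*Protocol article*

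**What the plan says.** The restriction on controls is limited in time. Under Intervention (2.5) they are to "maintain their habitual physical activity level and not initiate RT during chemotherapy". Once chemotherapy is over, the same section says that "controls will be invited to a 2-week introduction to the same resistance-training program as the intervention group following completion of chemotherapy", and that they are "offered a 12-month membership at a local gym, free of charge". The stated purpose is to raise interest in taking part. The section does not say what the intervention arm is offered after chemotherapy.

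Study design (2.1) places T1 after chemotherapy and T2 six months later, and states: "The primary outcome for this study is muscle fiber size". Table 1 marks CSA at all three visits. Neither place names a primary time point.

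Statistical analyses (2.11) sets the principle: "Data will be analyzed according to the intention-to-treat principle". It then lists several methods, among them "two-way repeated-measures ANOVA or the comparable nonparametric test as necessary to examine differences between and within groups, at T0, T1, and T2". It does not mention the offer made to controls after chemotherapy. The Discussion says the analyses will give insight into "how RT could be used as a therapeutic measure to counteract immediate and long-term treatment side effects".

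**The concern.** A reader would ordinarily take the six-month comparison in a two-arm trial of RT against usual activity as a test of whether the benefit lasts. Here the control condition changes between T1 and T2. Controls are free to start RT, are introduced to the trial's own programme, and have gym access that can cover the whole interval. If many take it up, the arms may converge because controls gain, with nothing lost in the intervention arm. A small or absent T2 difference would then invite the wrong conclusion.

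The plan does not guard against this, because it gives T2 the same standing as T1 for the primary outcome and does not say what the T2 contrast estimates. Nor does it describe data from which uptake could be reconstructed. The training logbook (2.6) is described for the intervention period. The physical-activity measurement at T2 (2.10.4) covers seven days.

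**Working it through.** **Inputs.** Difference 898 μm² and SD 840 μm² (Sample size, 2.3), taken here as the between-arm difference and the SD of change. 25 recruited per arm (2.3). About 75% completion in the earlier training study (Discussion): 0.75 × 25 = 18.75, so 19 per arm is used. Assumed, because the document does not give them: two-sided alpha 0.05, equal correlation between visits, and the fraction *f* of the T1 difference still present at T2.

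**The plan's own figure.** With 898 and 840, a two-sided two-sample t test needs 15 per arm for 80% power and 24 for 95%. The plan states 10 and 16, which these inputs do not reproduce. That is a separate matter and does not decide this point: 25 per arm gives 96% power for the T1 change.

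**T1 change from baseline, 19 per arm.** Standard error = 840 × √(2/19) = 272.5. Noncentrality = 898 / 272.5 = 3.30 on 36 df. Power is about 89%. Nothing that happens after T1 enters this figure.

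**T1 adjusted for baseline.** With visit correlation 0.6, the SD at one visit is 840 / √(2 × 0.4) = 939 and the residual SD is 939 × √(1 − 0.36) = 751. Noncentrality = 898 / (751 × √(2/19)) = 3.68. Power is about 94%, or roughly 93 to 96% for correlations from 0.7 down to 0.5.

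**T2 change alone.** Noncentrality = *f* × 3.30.

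**Three-visit group-by-time interaction.** λ = (n/2) × Σ(δₖ − mean δ)² / (840²/2), on 2 and 72 df. For *f* = 1 the differences are 0, 898, 898 and λ = 9.5 × 537,603 / 352,800 = 14.5. For *f* = 0.5 they are 0, 898, 449 and λ = 9.5 × 403,202 / 352,800 = 10.9. For *f* = 0, λ returns to 14.5.

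**Average of T1 and T2 minus T0.** Difference = 898 × (1 + *f*)/2. SD = 840 × √0.75 = 727.5.

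Power at 19 per arm:

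| T2 difference as share of T1 | 100% | 50% | 25% | 0% |
|---|---|---|---|---|
| T1 change | 89% | 89% | 89% | 89% |
| T2 change | 89% | 36% | 13% | 5% |
| Group-by-time interaction | 93% | 83% | 86% | 93% |
| Average of T1 and T2 | 96% | 79% | 64% | 46% |

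At 25 per arm the T1 change has 96%, and the T2 change 96, 46, 15 and 5%.

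The T2 comparison is thus the one that control uptake damages. The interaction loses at most about 6 points against the T1 change (89% to 83%), and it gains when the T2 difference is wholly kept or wholly lost. Serious dilution arises only if T1 and T2 are averaged.

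**The case against.** The other side has several good points.

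- **Dilution of the main test.** A reader might infer that T1 and T2 are pooled and the main test badly diluted. The document does not say so. A repeated-measures ANOVA keeps visits as separate levels, t tests are also listed, and section 2.11 does not say which effect is tested. For the interaction the loss is small.
- **An offer to controls alone.** This too is an inference. Section 2.5 describes an offer to controls and is silent on the other arm.
- **No evidence of a lasting effect possible.** This goes too far. T2 remains a valid randomised comparison of two strategies. If control training narrows the gap, a T2 difference still favouring RT would be conservative evidence of persistence.
- **Long-term claim.** The three hypotheses concern chemotherapy and RT during it. The long-term phrase is a Discussion sentence, not a planned inference at T2.
- **T1 already signalled, or left to the analysis plan.** The design is described as having follow-up at six months, and the Table 1 notes place T1 after the training intervention. A separate analysis plan may name the primary contrast.
- **Control training before the T1 biopsy.** T1 and the introduction are both placed only after chemotherapy, so this order is a possible reading. Nothing states that it happens, and no figure suggests that two introductory weeks would change CSA.

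These points remove the stronger readings. They leave one thing standing: a design feature that the protocol itself states changes what T2 estimates, and neither the analysis section nor the Discussion takes account of it.

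**Conclusion.** The point holds as a cheap improvement. At T2 the trial compares RT during chemotherapy with delayed access to RT, and a null or reversed T2 difference cannot be read as loss of benefit. In the illustration, T2-only power falls from about 89% to 36, 13 or 5% as the difference shrinks to a half, a quarter or nothing. The T1 comparison is untouched and gains about 5 points from baseline adjustment.

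These sizes rest on 19 per arm, an SD of change of 840, equal correlation between visits and two-sided 0.05. The T2 fractions are illustrations, since control uptake is not given. RT by the intervention arm after T1 is not described either, and it would also bear on how T2 is read.

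**What to change.** 1. In 2.1 and 2.11, name the between-group difference in CSA at T1, adjusted for baseline, as the primary comparison.
2. Make T2 secondary, described as RT during chemotherapy versus delayed access to RT, and word the Discussion's long-term statement to match.
3. Record RT between T1 and T2 in both arms and report it by arm.
4. State that controls' T1 assessments are completed before their RT introduction.

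The offer to controls can stay. The cost is a few sentences and one short training question at T2. The downside is that T2 cannot carry a confirmatory claim of RT versus no RT; under the design as described, it could not do so anyway.

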### Physical training logbook

2.6

To control for physical activity level during the intervention all participants will be instructed to keep a logbook of all physical training. Participants in the intervention group will be instructed to record all endurance training lasting more than 10 minutes with a perceived exertion of 15 (strenuous) or higher on the Borg-scale^[28]^ and any additional RT session performed. Participants in the control group are instructed to record all endurance training lasting more than 10 minutes with a perceived exertion of 15 (strenuous) or higher on the Borg-scale (29) and all resistance-training sessions.

### Muscle biopsy procedure

2.7

Muscle biopsies are obtained from the mid-section of *m. vastus lateralis* under local anaesthesia (Xylocain adrenaline, 10 mg ml^−1^ + 5 μg ml^−1^, AstraZeneca, Södertälje, Sweden). Briefly, a 1 to 2 cm incision will be made in the skin and the fascia of *m. vastus lateralis*. Biopsies are collected using a 6 mm Pelomi-needle (Albertslund, Denmark; Bergström technique) with manual suction to obtain muscle samples (≈200 mg). Biopsies will be rinsed in ice-cold saline 0.9% NaCl (Braun, Melsungen, Germany) and carefully dissected free of visual fat, connective tissue and blood. All pieces but 1 will be frozen in isopentane, precooled on dry ice, and stored at −80°C for later analysis. The last piece (≈10 mg) will be transferred to 500 μl RNA*later* Stabilization Solution (Invitrogen, Carlsbad, CA) and stored at +4°C for at least 24 hours before being transferred to −20°C for long-time storage.

